### Clinical randomized controlled trial

The clinical RCT consists of 1 month run-in and 3 months intervention. Time profile from baseline to the end of follow-up will be assessed (Fig. 1).

**Fig. 1 Fig1:**
[figure not shown]
Flow-chart of study

### Run-in

The participants will fill in a validated diagnostic paper headache diary one month prior to intervention which will be used as baseline data for all participants (Russell et al. 1992; Lundqvist et al. 2009). The validated diary includes questions directly related to the primary and secondary end-points. X-rays will be taken in standing position in the anterior–posterior and lateral planes of the entire spine. The X-rays will be assessed by the clinical investigator.

### Randomization

Prepared sealed lots with the three interventions, i.e., active treatment, placebo and the control group, will be divided into four sub-groups by age and gender, i.e., woman and men, 18–39 and 40–70 years, respectively. Participants will be equally allocated to one of the three arms by only allowing participants to draw one lot. The blocked randomization will be administrated by an external trained party without the involvement from the clinical investigator.

### Intervention

Active treatment consists of CSMT using the Gonstead method (Cooperstein 2003). A specific contact, high-velocity, low-amplitude, short-lever, with no recoil post spinal adjustment directed to spinal biomechanical dysfunction diagnosed by standard chiropractic tests.

The placebo intervention consists of sham manipulation, i.e., a broad non-specific contact, low-velocity, low-amplitude sham push manoeuvre in a non-intentional and non-therapeutic directional line. All the non-therapeutic contacts will be performed outside the spinal column with adequate joint slack and without pre-tension so no joint cavitations occur (Chaibi et al. 2015). In some sessions, the participant lay either prone on a Zenith 2010 HYLO bench with the investigators standing at the participant’s right side with his left palm placed on the participant’s right lateral scapular edge with the other hand reinforcing. In other sessions, the investigator will stand at the participant’s left side and place his right palm over the participant’s left scapular edge with the other hand reinforcing, delivering a non-intentional lateral push manoeuvre. Alternatively, the participant lay in the same side posture position as the active treatment group with the bottom leg straight and top leg flexed with top leg’s ankle resting on the bottom leg’s knee fold, in preparation for a side posture push move, which will be delivered as a non-intentional push in the gluteal region. The sham manipulation alternatives will be equally interchanged among the placebo participant’s according to protocol during the 12 weeks treatment period to strengthen the study validity. Both the active and the placebo group will receive the same structural and motion assessment prior to and after each intervention. No additional co-interventions or advises will be given to participants during the trial period. The treatment period will include 12 consultations, i.e., twice per week the first three weeks followed by once a week the next two and once every second week until 12 weeks are reached. Fifteen minutes will be allocated per consultation for each participant. All interventions will be administered by an experienced chiropractor (AC) at Akershus University Hospital and Innlandet Hospital Trust, Norway.

The control group will continue usual care, i.e., pharmacological management without receiving manual intervention by the clinical investigator. The same exclusion criteria apply for the control group during the whole study period.

### Blinding

Participants whom receive active or placebo intervention will fill in a de-blinding questionnaire after each of the 12 treatment sessions administrated by an external trained independent party with no involvement from the clinical investigator, i.e., providing a dichotomous “yes” or “no” answer as to the question whether active treatment was received. This response was followed by a second question regarding how certain they were that active treatment was received on a 0–10 numeric rating scale (NRS), where 0 represents absolutely uncertain and 10 represents absolute certainty. The control group and the clinical investigator can for obvious reasons not be blinded (Bang et al. 2004; Johnson 2005; Chaibi et al. 2015).

### Follow-up

Follow-up analysis will be conducted on the end-points measured after the end of intervention and 3, 6 and 12 months follow-up. During this period all participants will continue to fill in a diagnostic headache diary and return it on a monthly basis. In the case of unreturned diary or missing values in the diary, the participants will be contacted immediately upon detection to minimize recall bias. Participants will be contacted by phone to secure compliance.

### Primary and secondary end-points

The primary and secondary end-points are listed in Table 2. The end-points adhere to the recommended IHS clinical trial guidelines (Tfelt-Hansen et al. 2000; Silberstein et al. 2008). We define number of headache days to be primary end-point and expect at least 25 % reduction in average number of days from baseline to the end of intervention, with the same level of reduction maintaining at follow-up. Based on previous reviews on CEH, a 25 % reduction is considered to be a conservative estimate (Chaibi and Russell 2012). A 25 % reduction from baseline to the end of intervention and follow-up is also expected in secondary end-points for headache duration, headache intensity, and headache index, where the index is calculated as mean days with headache (30 days) × mean headache duration (hours per day) × mean intensity (0–10 NRS). A 50 % reduction in medication consumption from baseline to the end of intervention and to follow-up is expected.

**Table 2 Tab2:** Primary and secondary end-points

Primary end-points
1. Number of headache days in active treatment vs. placebo group
2. Number of headache days in active treatment vs. control group
Secondary end-points
3. Headache duration in hours in active treatment vs. placebo group
4. Headache duration in hours in active treatment vs. control group
5. Self-reported VAS in active treatment vs. placebo group
6. Self-reported VAS in active treatment vs. control group
7. Headache index (frequency × duration × intensity) in active treatment vs. placebo group
8. Headache index in active treatment vs. control group
9. Headache medication dosage in active treatment vs. placebo group
10. Headache medication dosage in active treatment vs. control group

The data analysis is based on the run-in period vs. end of intervention. Point 11–40 will be duplicate of point 1–10 above at respectively 3, 6 and 12 months follow-up

### Data processing

A flowchart of the participants is shown in Fig. 2. Baseline demographic and clinical characteristics will be tabulated as means and standard deviations (SD) for continuous variables and proportions and percentages for categorical variables. Each of three groups will be described separately. Primary and secondary end-points will be presented by suitable descriptive statistics in each group and for each time point. Normality of end-points will be assessed graphically and transformation will be considered if necessary.

**Fig. 2 Fig2:**
[figure not shown]
Expected participants flow diagram

Change in primary and secondary end-points from baseline to the end of intervention and to follow-up will be compared between active and placebo and active and control group. Null-hypothesis states that there is no significant difference between the groups in average change, while the alternative hypothesis states that a difference of at least 25 % exists.

Due to follow-up period, repeated recordings of primary and secondary end-points will be available, and analyses of trend in primary and secondary end-points will be of main interest. Intra-individual correlations (cluster effect) are likely to be present in data with repeated measurements. Cluster effect will thus be assessed by an intra-class correlation coefficient (ICC) quantifying the proportion of total variation attributable to the intra-individual variations. The trend in end-points will be assessed by a linear regression model for longitudinal data (linear mixed model) to correctly account for possible cluster effect. Linear mixed model handles unbalanced data, enabling all available information from randomized patients to be included, also from drop-outs. Regression models with fixed effects for time component and group allocation as well as the interaction between the two will be estimated. The interaction will quantify possible differences between groups regarding time trend in the end-points and serve as an omnibus test. Random effects for patients will be included to adjust the estimates for intra-individual correlations. Random slopes will be considered. The linear mixed models will be estimated by SAS PROC MIXED procedure. The two pairwise comparisons will be performed by deriving individual time point contrasts within each group with the corresponding p values and 95 % confidence intervals (CI).

Both per-protocol and intention-to-treat analyses will be conducted if relevant. All analyses will be performed by a statistician, blinded for group allocation and participants. All adverse effects will also be registered and presented. Participants who experience any sort of adverse effects during the trial period will be entitled to call the prime investigator on the project cell phone. The data will be analyzed with SPSS v22 and SAS v9.3. Because of two group-comparisons in a primary end-point, p values below 0.025 will be considered statistically significant. For all secondary end-points and analyses, a significance level of 0.05 will be used. Missing values might appear in incomplete interview questionnaires, incomplete headache diaries, missed intervention sessions and/or due to drop-outs. The pattern of missingness will be assessed and missing values handled adequately.

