## Methods and design

This is a single-blinded placebo-controlled RCT with three parallel groups (CSMT, placebo and control). Our primary hypothesis is that CSMT gives at least 25 % reduction in average number of headache days per month (30 days) as compared to no change in the placebo and the control group from baseline to the end of intervention, and we expect the same reduction to maintain at 3, 6 and 12 months follow-up. If the CSMT treatment is effective, it will be offered to participants whom received placebo or control after study completion, i.e., after 12 months follow-up. The study will adhere to the recommended clinical trial guidelines from the IHS (Tfelt-Hansen et al. 2000; Silberstein et al. 2008), and the methodological CONSORT guidelines (Moher et al. 2010).

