### Power calculation

Sample size calculations are based on the results in a recently published group comparison study on topiramate (Silberstein et al. 2004). We hypothesize that the mean difference in reduction of number of days with headache per month between active and the placebo group is 2.5 days. The same difference is assumed between active and the control group. Standard deviation for reduction in each group is assumed to be equal 2.5. Under the assumption of on average 10 headache days per month at baseline in each group and no change in the placebo or control group during the study, 2.5 days reduction corresponds to a reduction by 25 %. As primary analysis includes two group-comparisons, we set a significance level at 0.025. A sample size of 20 patients is required in each group to detect a statistical significant mean difference in reduction of 25 % with 80 % power. To allow for drop-outs, the investigators plan to recruit at least 120 participants.

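### The alternative hypothesis is a difference of at least 25 %, but the planned test and sample size address only whether the difference is zero

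*Protocol article*

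**What the plan says.** Data processing gives the hypotheses for change in the primary and secondary end-points. The null reads "Null-hypothesis states that there is no significant difference between the groups in average change". The opposing statement sets a threshold of 25 %: "the alternative hypothesis states that a difference of at least" that size. Methods and design puts the same figure into the main hypothesis: "Our primary hypothesis is that CSMT gives at least" 25 % reduction in headache days, against no change in placebo and control.

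The analysis is a linear mixed model with a group-by-time interaction, followed by contrasts: "The two pairwise comparisons will be performed by deriving individual time point contrasts within each group with the corresponding p values". Confidence intervals at the 95 % level accompany them. For the primary end-point, "p values below 0.025 will be considered statistically significant". No margin, shifted null or confidence-limit criterion is stated.

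Power calculation takes a difference of 2.5 days and an SD of 2.5 days, and says "we set a significance level at 0.025". It concludes that a sample of 20 "is required in each group to detect a statistical significant mean difference in reduction" of 25 % with 80 % power. It makes clear that 2.5 days equals 25 % on the assumption of 10 headache days at baseline and no change in the comparators. At least 120 participants are to be recruited to allow for drop-outs.

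**The concern.** A null and an alternative should together cover the possible true values, and both should be statements about the population. Here a true difference of, say, 15 % belongs to neither hypothesis, and the null refers to significance, which is an outcome of the test.

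The larger difficulty is what a rejection would mean. Taken as written, rejecting the null leads to the alternative, that is, to a difference of at least 25 %. The planned test can only show that the difference is not zero. The hypothesis section therefore attaches to a positive result a conclusion that the test does not deliver. What is at stake is the wording of the trial's main conclusion.

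**Working it through.** **Inputs.** Power calculation: difference 2.5 days, SD of the reduction 2.5 days in each group, significance level 0.025 per comparison, power 80 %, baseline 10 days, 20 per group, at least 120 recruited. Randomization: equal allocation to three arms, so 120/3 = 40 per arm. Sidedness is not stated.

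**1. Which test does the stated sample size belong to?** Two-sided test of zero difference, normal approximation:

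n = 2 × (z₀.₉₈₇₅ + z₀.₈₀)² × (SD/difference)² = 2 × (2.241 + 0.842)² × (2.5/2.5)² = 19.0, rounded up to 20.

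This reproduces the protocol's figure. A one-sided 0.025 test, or a two-sided 0.05 test, would give 16. With the t distribution, power at 20 per group is 79.3 %, and 21 per group passes 80 %. So the sample size is that of a two-sided test at 0.025 against zero, with 25 % as the effect to be detected.

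**2. What is the smallest observed difference that is significant?** Two-sample t test on change: d = t(0.9875; 2n − 2) × SD × √(2/n).

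| Analysed per arm | t quantile | SE (days) | Smallest significant difference | Share of 10 days |
|---|---|---|---|---|
| 20 | 2.334 | 0.791 | 1.84 days | 18 % |
| 40 (no drop-outs) | 2.286 | 0.559 | 1.28 days | 13 % |

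**3. How often would a smaller true effect be significant?** At a true difference of 1.5 days (15 % of 10; an illustrative value), p falls below 0.025 with probability 34 % at 20 per arm and 65 % at 40 per arm. Such a result would be correct as a rejection of zero, but the difference would not be 25 %.

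**4. What would support a claim of at least 2.5 days?** The interval that matches a two-sided 0.025 test is the 97.5 % interval, whose half-widths are the values in step 2. Its lower limit exceeds 2.5 days only if the observed difference exceeds 2.5 + 1.84 = 4.34 days (20 per arm) or 2.5 + 1.28 = 3.78 days (40 per arm).

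**5. Side note on the headache index.** Primary and secondary end-points defines the index as mean days × mean duration × mean intensity. It expects at least a 25 % fall in days, and the same percentage for three others: "reduction from baseline to the end of intervention and follow-up is also expected in secondary end-points for headache duration, headache intensity, and headache index". If all three components fall by 25 %, the index falls by 1 − 0.75³ = 1 − 0.422 = 57.8 %, about 58 %. A 25 % fall in the index needs only 1 − 0.75^(1/3) = 9.1 % in each component.

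**The case against.** The strongest defence is that nothing operative is wrong. Test, significance level and sample size agree with one another, and naming the design effect in the alternative is common shorthand. Power calculation openly gives the 10-day baseline and unchanged comparators as assumptions. Confidence intervals are planned, so readers could see whether smaller differences are excluded. In any trial with 80 % power the smallest significant difference lies below the design effect; here, at 20 per arm, it is 1.84/2.5 = 74 % of it. All of this stands. It limits the point to the hypotheses and the conclusion drawn from them. It does not rescue the pair as written, because the article gives at least 25 % both as the formal alternative and as the primary hypothesis, not merely as a planning value.

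A reader might infer more than the documents support:

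- **That the authors will report any significant p value as confirming 25 %.** No section says so. The stated rule is only that such a p value counts as statistically significant.
- **That significance could rest on only half the planned effect.** This takes 1.28/2.5 = 51 %, which requires all 40 per arm to be analysable, although 120 are recruited precisely to allow for drop-outs.
- **That the design is specially weak because a true difference of exactly 2.5 days would clear a 2.5-day bound in only 1.25 % of trials.** That holds by construction in any trial whose true value equals the bound, and says nothing particular about this one.
- **That the index target contradicts its components.** The paragraph presents 25 % as a conservative estimate for headache days. Read likewise as a floor for the index, it is met by a 58 % fall. No test, success criterion or sample size uses it.

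**Conclusion.** The hypothesis statement is wrong as written. The two hypotheses omit differences between 0 and 25 %, the null is phrased as a test result, and the alternative claims more than a rejection of zero can show. The gap is material on the protocol's own figures: significance begins at 18 % of the assumed baseline with 20 per arm and at 13 % with 40 per arm.

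These figures assume an SD of 2.5 days, a 10-day baseline, no change in the comparators and a simple two-sample comparison of change. The mixed-model contrast may differ somewhat in precision. The sample size is consistent with a test of zero difference, and neither it nor the analysis is at fault.

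The index expectation is a minor matter. It is much weaker than its components imply, and no analysis depends on it. The 58 % is exact for a product of means; an index averaged over participants with unequal changes could differ.

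**What to change.** In Data processing, state for each primary comparison: H0, the between-group difference in mean change in headache days is zero; H1, it is not zero. Reword the primary hypothesis in Methods and design to match, keeping 2.5 days (25 % of an assumed 10-day baseline) as the planning effect only.

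Add that a reduction of at least 2.5 days will be claimed only if the confidence limit at the level matching the 0.025 test excludes smaller differences. This means reporting a 97.5 % interval for the two primary comparisons, since the planned 95 % interval does not correspond to that test.

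In Primary and secondary end-points, label the 25 % for the headache index as a floor, or drop it.

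The cost is wording and one additional interval for each primary comparison; sample size and analysis model do not change. The drawback is that the stronger claim will seldom be available: on the protocol's assumptions it needs an observed difference above 3.78 days even with 40 per arm.

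### The mixed model lets each arm have its own run-in mean, so its contrasts reduce to change-score differences and give up some precision that the run-in diary could supply

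*Protocol article*

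**What the plan says.** Data processing (the text after Fig. 2) gives the target of the comparison: "Change in primary and secondary end-points from baseline to the end of intervention and to follow-up will be compared between active and placebo and active" (the second pair is completed by the control arm). The model is then described: "Regression models with fixed effects for time component and group allocation as well as the interaction between the two will be estimated". On the covariance side: "Random effects for patients will be included to adjust the estimates for intra-individual correlations. Random slopes will be considered". The interaction serves as the omnibus test, and the pairwise comparisons come from time-point contrasts.

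Run-in says of the one-month diary "which will be used as baseline data for all participants". The note under Table 2 bases the analysis on run-in against end of intervention, repeated at 3, 6 and 12 months.

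Under Randomization, the lots "will be divided into four sub-groups by age and gender, i.e., woman and men, 18–39 and 40–70 years, respectively", and the allocation is blocked and equal across the three arms.

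The article nowhere enters run-in headache days as a covariate, sets a common run-in mean, or puts age group and gender into the model.

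Power calculation uses a 2.5-day difference in reduction, an SD of 2.5 for the reduction, a significance level of 0.025 and 80 % power. It arrives at 20 per group and recruits at least 120.

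**The concern.** Randomization makes the arms' run-in means equal in expectation. A model with a group main effect at run-in does not use that fact. It estimates three separate run-in means and subtracts them, so the noise in each is carried at full weight into the treatment contrast. Baseline adjustment subtracts only the part that predicts the later value.

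Two things are at stake. The first is precision. The second is how the estimate behaves in the one allocation that is realised: if one arm happens to start with more headache days, regression to the mean shifts the change-score estimate by (1-rho) times that imbalance. Both can be avoided with data that the trial already collects.

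**Working it through.** **Inputs from the article.** Difference 2.5 days; SD of change 2.5; significance level 0.025 (taken as two-sided, which reproduces the stated sample size; one-sided gives 16); 20 per group; 120 recruited, so 40 per arm. Five time points: run-in, end of intervention, 3, 6 and 12 months.

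**Assumptions.** Time is categorical, the covariance is compound symmetric (a random intercept), and data are complete. Rho is not in the article, so a range is shown.

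**The plan's own figure.** n = 2(z₀.₉₈₇₅ + z₀.₈₀)² (SD/difference)² = 2(2.241 + 0.842)² × 1 = 19.01, rounded up to 20. This reproduces. By the noncentral t, power at 20 per group is 79.3 %.

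**Variance ratio.** Let s² be the variance of headache days at one time point.
- Change score: 2s²(1-rho)
- Common run-in mean, or run-in as covariate: s²(1-rho²)
- Ratio: (1+rho)/2

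Holding the change SD at 2.5, the effective SD is 2.5 × √((1+rho)/2). SE at 40 per arm is SD × √(2/40), so for the stated model 2.5 × 0.2236 = 0.559 days. Power is by noncentral t for a 2.5-day difference.

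| Assumed rho | Variance ratio | Effective SD | SE at 40 per arm | Power at 20 per arm | Power at 40 per arm |
|---|---|---|---|---|---|
| stated model | 1 | 2.50 | 0.559 | 79.3 % | 98.5 % |
| 0.5 | 0.75 | 2.17 | 0.484 | 90.1 % | 99.8 % |
| 0.7 | 0.85 | 2.30 | 0.515 | 85.9 % | 99.4 % |
| 0.8 | 0.90 | 2.37 | 0.530 | 83.7 % | 99.2 % |
| 0.9 | 0.95 | 2.44 | 0.545 | 81.4 % | 98.8 % |

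A generalised least squares calculation with five time points, three arms of 40 and four balanced strata confirms 0.559 for the stated model, and 0.484 and 0.515 at rho 0.5 and 0.7.

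**A smaller true difference.** If the difference were 1.5 days (an illustration, not a figure from the article), power at 40 per arm would go from 65.5 % to 79.0, 73.3, 70.6 and 68.0 % at rho 0.5, 0.7, 0.8 and 0.9.

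**Which rho is plausible.** Under compound symmetry s = 2.5/√(2(1-rho)), so a change SD of 2.5 implies a between-patient SD of 2.5 at rho 0.5, 3.2 at 0.7, 4.0 at 0.8 and 5.6 at 0.9. Turned round, assumed SDs of 4, 5 and 6 days give rho of about 0.80, 0.88 and 0.91. The gain is then worth 1/ratio - 1, about 11, 7 and 5 % more patients.

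**Chance imbalance.** At rho 0.5, s is 2.5, and the SE of the run-in difference at 20 per arm is 2.5 × √(2/20) = 0.79 days. A 1-day imbalance is therefore unremarkable, and it would shift the estimate by (1-0.5) × 1 = 0.5 days, a fifth of the target. At rho 0.8 the same imbalance shifts it by 0.2 days.

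**Strata.** Adding stratum main effects to the stated model leaves the SE at 0.559: a term that is constant over time cancels out of a change. With a common run-in mean, and strata assumed to explain 10 to 20 % of outcome variance, the SE goes from 0.484 to 0.475-0.464 at rho 0.5 and from 0.515 to 0.510-0.504 at rho 0.7. Over rho 0.3 to 0.7 that is a further 1 to 7 %.

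**The case against.** The stated model is valid. It matches the stated comparison (change from baseline) and the sample size, which rests on the SD of the reduction. The article is condensed, no analysis plan is shown, and it does not say that these are the only fixed effects. At the planned 40 per arm and 2.5 days, power is already 98.5 %, so adjustment can add at most about 1.5 points.

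Most of this stands and limits the weight of the point. It does not remove it: the article states a concrete set of fixed effects, an interaction test and contrasts, and that specification is the less efficient choice whenever rho is below 1.

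Three stronger readings are tempting and are not supported.
- A reader might infer that leaving out the randomization strata makes the standard errors of the planned contrasts too large. With complete data it does not: adding stratum main effects to the stated model leaves the SE unchanged.
- A reader might infer from entry at one headache attack per month (Patient population) that run-in values vary widely and that the gain is therefore large. The inference runs the other way. With the change SD fixed at 2.5, a wide spread implies a high rho and a gain of only about 5 to 11 % more patients.
- A reader might infer bias. Over randomization there is none; the shift from imbalance is conditional on one realised allocation.

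**Conclusion.** This is an efficiency point of modest and partly unknown size, not an error of validity. The contrast variance would fall by 25 % at rho 0.5 and by 5 % at rho 0.9.

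The practical gain is negligible if most of the 120 stay and the difference is 2.5 days. It matters if drop-out approaches the half that recruiting 120 against 60 allows for, or if the true difference is smaller. The article makes both conceivable. Methodological considerations warns of increased loss to follow-up. It also expects a high placebo response, perhaps higher with physical contact, whereas Power calculation assumes no change under placebo.

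The figures rest on categorical time, compound symmetry, complete data and assumed rho. Random slopes, which the article leaves open, or a linear time trend would alter them. The contribution of the strata is secondary and depends on prognostic strength that the article does not report.

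**What to change.** In Data processing, keep run-in as the first response but constrain the three arms to one common run-in mean, by omitting the group effect at that time point. Equivalently in purpose, model the post-baseline headache days with run-in days as a covariate. Use the same form for the secondary end-points.

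Together with this, add the four age-by-gender strata as fixed effects, preferably also by time. Strata without the baseline change would bring no precision to these contrasts with complete data.

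The cost is one sentence and a small change to the model code, with no new data. The sample size can stay as it is, since it takes no credit for baseline adjustment. The change should be fixed before the data are unblinded.

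### The primary time-point contrasts rest on a patient random effect with no residual structure named; an unstructured covariance would protect the 0.025 tests whatever the correlation pattern

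*Protocol article*

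**What the plan says.** All references are to the protocol article, Methods and design.

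- **Hypothesis (Data processing).** "Null-hypothesis states that there is no significant difference between the groups in average change". The target is therefore a mean change from run-in, and the null does not require every patient to change by the same amount.
- **Model (Data processing).** A linear mixed model in SAS PROC MIXED with fixed effects for time, group and their interaction. On correlation: "Random effects for patients will be included to adjust the estimates for intra-individual correlations. Random slopes will be considered". The clustering is to be summarised by one ICC. No residual (repeated) structure is named, and no rule says when slopes enter.
- **Primary test (Data processing).** The two pairwise comparisons are time-point contrasts from this model. Each is judged at 0.025.
- **Time course (Primary and secondary end-points).** A mean reduction by the end of intervention, "with the same level of reduction maintaining at follow-up".
- **Sizing (Power calculation).** "Standard deviation for reduction in each group is assumed to be equal 2.5" and "As primary analysis includes two group-comparisons, we set a significance level at 0.025". The target is a "mean difference in reduction of number of days with headache per month between active and the placebo group is 2.5 days", and "A sample size of 20 patients is required in each group to detect a statistical significant mean difference in reduction of 25 % with 80 % power". On recruitment: "To allow for drop-outs, the investigators plan to recruit at least 120 participants".

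**The concern.** A patient random intercept with independent residuals gives any two visits the same correlation and every change from baseline the same variance. The standard error of the primary contrast then comes from a residual variance averaged over run-in, end of intervention and 3, 6 and 12 months. It does not come from the observed spread of patients' changes to the end of intervention.

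Two ordinary departures matter, and they act in opposite directions on the primary contrast:

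- **Lasting individual response.** If some patients drop and stay down while others do not, post-treatment visits correlate more with each other than with run-in. The standard error is then too small, and chance differences are declared significant too often.
- **Fading correlation.** If visits further apart are less alike, the pooled variance is too large for the short step from run-in to end of intervention, and a real difference can be missed. For the long step to the 12-month follow-up it is too small.

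The p-values judged against 0.025 and the reported confidence intervals both depend on this.

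**Working it through.** **Inputs from the protocol.** Difference 2.5 days; SD of change 2.5, so variance of change 6.25; level 0.025 (two-sided reproduces the stated n); 20 per arm required; 120 recruited, so 40 per arm; analysis points at months 0, 3, 6, 9 and 15.

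**Assumed.** Complete data, categorical time, independent residuals, and the covariance scenarios below. None of the scenarios is in the documents.

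**1. The plan's own figure.** n = 2(2.241 + 0.842)² × 6.25 / 2.5² = 19.0, which rounds up to 20 per arm. It reproduces. At 20 per arm the SE is √(2 × 6.25/20) = 0.791 and 2.5/0.791 = 3.162, so power is Φ(3.162 − 2.241) = 82.1 % (79.3 % by the noncentral t). At 40 per arm, 2.5/SE = 4.472 and power is 98.7 %.

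**2. General formula.** With complete data the contrast is the difference in raw mean changes under either covariance model; only the SE differs. Let r = model SE / true SE. Then actual level = 2[1 − Φ(2.241 r)] and power = Φ(2.5/SE − 2.241 r).

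**3. Lasting response.** Let a share s of the 6.25 be a patient-specific shift present at all four post-treatment visits, with variance s_d² = 6.25 s, and let visit noise satisfy 2s_e² = 6.25(1 − s). The pooled within-patient variance over five visits is s_e² + 0.2 s_d², so the model variance of change is 6.25(1 − 0.6 s) and r = √(1 − 0.6 s). For s = 0.5 this is 2(1.5625 + 0.625) = 4.375 against 6.25.

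| s | r | Actual level | Coverage of 95 % CI | Level with linear slope added |
|---|---|---|---|---|
| 0 | 1.000 | 2.5 % | 95 % | 2.5 % |
| 0.25 | 0.922 | 3.9 % | 93 % | 4.1 % |
| 0.50 | 0.837 | 6.1 % | 90 % | 6.8 % |
| 0.75 | 0.742 | 9.7 % | 85 % | 11.5 % |

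The slope column comes from fitting intercept plus linear slope to the true covariance by maximum likelihood. A drop followed by a plateau is not a straight line, so the slope does not help. The ratio r does not involve n. Simulation of the random-intercept model at s = 0.5 gave 6.0 % at 20 per arm and 5.7 % at 40.

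**4. Fading correlation.** Let the correlation be ρ to the power of the months apart, scaled so that the change to month 3 still has variance 6.25. The ten visit pairs have lags 3 (three pairs), 6 (three), 9 (two), 12 and 15. Then r² = (1 − mean pairwise correlation)/(1 − ρ³).

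- ρ = 0.90: mean correlation 0.504, r² = 0.496/0.271, r = 1.352.
- ρ = 0.95: mean correlation 0.704, r² = 0.296/0.143, r = 1.440.

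| End-of-intervention power | Correct SE | ρ = 0.90 | ρ = 0.95 |
|---|---|---|---|
| Intercept only, 20 per arm | 82 % | 55 % | 47 % |
| Intercept only, 40 per arm | 98.7 % | 92.5 % | 89 % |
| Slope added, 20 per arm | 82 % | 72 % | 71 % |
| Slope added, 40 per arm | 98.7 % | 97 % | 97 % |

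For the 12-month follow-up contrast, replace 1 − ρ³ by 1 − ρ¹⁵. The intercept-only level is then 7.7 % (ρ = 0.90) or 9.6 % (ρ = 0.95).

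**5. Variance of change left free.** In simulation the level was 2.2–2.7 % and power about 80 % at 20 per arm in every scenario. When the exchangeable model was true, power was 80.0 % against 81.9 %.

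**The case against.** The strongest reply is that this is detail for an analysis plan that is not shown. The article says nothing on residual structure, so independent residuals are a reading of its silence. That stands in part: the figures apply to the model taken as written, and a later plan may name something safer. It does not remove the point, because the article does name its device for within-patient correlation, and an alternative in the same procedure is more robust for the contrast it wants.

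Three stronger readings are tempting, and the documents do not support them.

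- **That the plan assumes patients do not differ in response.** It says slopes will be considered, which provides for individual change. The limit is that a linear slope fits a step-and-hold pattern badly.
- **That the expected maintained reduction contradicts equal correlation.** The expectation concerns group means, which the time-by-group terms handle. A mean drop that holds is compatible with equally correlated visits. The same applies to the high placebo response mentioned in the Discussion.
- **That one flaw both inflates error and costs 27–35 points of power.** Lasting response raises the rejection rate and so does not lose power. The loss needs fading correlation, 20 evaluable per arm and no slope.

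**Conclusion.** The point holds as a robustness weakness whose size the documents cannot fix. They give only the SD of change; the split between lasting response and visit noise, and any fading, are assumed. On those assumptions, at the end of intervention:

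- **Type I error:** about 4–10 % instead of 2.5 % for lasting shares of 25–75 %, at either sample size and not repaired by a linear slope.
- **Power:** under fading, 27–35 points lost at 20 per arm and 6–9 at 40 with intercept only; with a slope, about 10–11 and 2 points.
- **Neither feature present:** exactly 2.5 %.

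A reader might infer that the trial's true error rate is known to be several times nominal. It is not: it could be correct. The type I result deserves more weight than the power result, because recruiting 120 does not reduce it. The change is worth making before the primary analysis, since it removes the dependence on an untested correlation pattern and an open choice about slopes.

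**What to change.** In Data processing, replace the two sentences on random effects and slopes with wording such as: *Time will be categorical (run-in, end of intervention, 3, 6 and 12 months). For the time-point contrasts, within-patient covariance will be unstructured (PROC MIXED, REPEATED / TYPE=UN, REML, Kenward-Roger degrees of freedom). If this does not converge, a heterogeneous Toeplitz structure with empirical standard errors will be used.* The unstructured matrix takes the place of the patient random effect and is not added to it. Another simpler fallback would serve if it is fixed in advance. The ICC may stay as a descriptive statistic.

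Cost: wording only, in software already named. The model estimates 5 × 6/2 = 15 covariance parameters instead of 2, which is manageable with 60–120 patients. It gives up about 2 points of power at 20 per arm if the exchangeable model is true.
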